## Abstract

**Background:**

Delirium is a state of confusion characterized by an acute and fluctuating decline in cognitive functioning. Delirium is common and deadly in older adults with dementia, and is often referred to as delirium superimposed on dementia, or DSD. Interventions that treat DSD are not well-developed because the mechanisms involved in its etiology are not completely understood. We have developed a theory-based intervention for DSD that is derived from the literature on cognitive reserve and based on our prior interdisciplinary work on delirium, recreational activities, and cognitive stimulation in people with dementia. Our preliminary work indicate that use of simple, cognitively stimulating activities may help resolve delirium by helping to focus inattention, the primary neuropsychological deficit in delirium. Our primary aim in this trial is to test the efficacy of Recreational Stimulation for Elders as a Vehicle to resolve DSD (RESERVE- DSD).

**Methods/Design:**

This randomized repeated measures clinical trial will involve participants being recruited and enrolled at the time of admission to post acute care. We will randomize 256 subjects to intervention (RESERVE-DSD) or control (usual care). Intervention subjects will receive 30-minute sessions of tailored cognitively stimulating recreational activities for up to 30 days. We hypothesize that subjects who receive RESERVE-DSD will have: decreased severity and duration of delirium; greater gains in attention, orientation, memory, abstract thinking, and executive functioning; and greater gains in physical function compared to subjects with DSD who receive usual care. We will also evaluate potential moderators of intervention efficacy (lifetime of complex mental activities and APOE status). Our secondary aim is to describe the costs associated with RESERVE-DSD.

**Discussion:**

Our theory-based intervention, which uses simple, inexpensive recreational activities for delivering cognitive stimulation, is innovative because, to our knowledge it has not been tested as a treatment for DSD. This novel intervention for DSD builds on our prior delirium, recreational activity and cognitive stimulation research, and draws support from cognitive reserve theory.

**Trial registration:**

ClinicalTrials.gov identifier: NCT01267682

## Background

Delirium is a state of confusion characterized by an acute and fluctuating decline in cognitive functioning[1]. The exact cause of delirium is unknown but typically involves a vulnerable patient and a noxious insult such as surgery, infection, or adverse effects from medications[2]. Delirium is common and deadly in older adults with dementia, and is often referred to as delirium superimposed on dementia, or DSD. Over 80% of older adults with dementia experience delirium when hospitalized, and studies report that between 24 and 76% die within one year of the index episode [3,4]. Delirium often persists long past the acute phase of an illness and substantially worsens outcomes in a population already burdened with physical and cognitive deficits [5,6]. Over two thirds of older adults admitted to post acute care exhibit delirium on admission[7]. Unresolved delirium results in an accelerated trajectory of cognitive and physical decline that prolongs hospitalization and rehabilitation, and precipitates premature nursing home placement [4,8-10].

It is difficult to prevent delirium in persons who already have reduced cognitive reserve [11]. Efforts to resolve established delirium are critical to implement because data indicate that when delirium resolves slowly, or never at all, less than 50% of pre-illness functioning is realized[12]. These individuals are at high risk for poor quality of life and institutionalization because of their resultant functional impairments, their care becoming too burdensome for family caregivers to support. Interventions that slow the accelerated downward spiral accompanying DSD have the potential to make a major public health impact by preserving function, preventing premature institutionalization and reducing the $152 billion national burden attributed to delirium [4,13,14].

Unfortunately, interventions that treat DSD are not well-developed because the mechanisms involved in its etiology are not completely understood. Historically, the pathophysiology of delirium has been characterized as a derangement of the functional metabolism of the brain[15]. In support of this theory, studies have found decreased blood flow in varied and diffuse regions of the brain that normalizes once the delirium resolves[16,17]. On a cellular level there is disruption of cholinergic transmission[2,18], dopaminergic excess[19], and elevated markers of inflammation (chemokines and cytokines)[20].

The primary neuropsychological deficit in delirium is in the domain of attention; orientation, memory, abstract thinking and executive function are also affected[21]. These deficits are responsible for the cognitive decline seen in delirium, and as improvement in these domains occurs, the fluctuating course typical of delirium resolves[22,23].

Deficits in physical function, i.e., activities of daily living (ADLs) and instrumental activities of daily living (IADLs) parallel the changes in cognition that accompany delirium[4,24-26]. Attentional impairments adversely affect memory performance and may underlie the impaired ADLs and IADLs seen in delirium [27,28]. Attentional impairments affect loco-motor function and increase the risk of falls and accidents [28-30]. Individuals who experience the acute cognitive problems associated with delirium are likely to experience problems with continence, ambulation, dressing, and general way-finding, among other functional tasks.

Very few studies have examined unique risk factors for delirium in persons with dementia, although the available evidence seems to indicate that they are similar to factors observed in cognitively intact individuals. Voyer and colleagues found that advanced age, dementia severity, pain, depression, dehydration, function, behavior, number of medications, and fever were all predisposing risk factors for DSD[31]. In a retrospective chart review of 199 patients with Alzheimer's Disease (AD), urinary tract infection (UTI), surgery, stress/bereavement (death of spouse, change in residence), and severe pain occurred more frequently in delirious than non-delirious patients[32]. Using administrative data, our retrospective review of 7,347 persons with dementia found that those with DSD were older and treated for higher rates of cerebrovascular disease, UTI, dehydration, and pneumonia[33]. Severity of delirium has been linked to later stages of dementia[23] and presence of depression[31].

Certain classes of medications are also strong risk factors for delirium. Persons with dementia take a greater number of central nervous system (CNS)-active medications than their cognitively intact counterparts, including antipsychotics, anxiolytics, and antidepressants[34]. These drugs are known to increase risk of delirium and further cognitive deterioration because of their potent anticholinergic properties [35,36]. Even CNS-active drugs that are appropriately used can accumulate in amounts that lead to delirium, sedation, and falls[37].

Also important for this study are data that indicate a relationship between presence of the apolipoprotein E (ApoE) *E4 allele and delirium severity and duration. Though findings have not always been consistent[38], the weight of the evidence indicates that having at least one copy of the *E4 allele is associated with an increased risk of delirium in young and older adults as well as a more protracted course, independent of demographic and clinical covariates, or premorbid cognitive impairments[39-42].

Clinical management of established delirium is quite variable and includes interventions that target risk factors associated with delirium, but there is no strong empirical basis for prescribing these interventions[43]. The results of clinical trials have been quite modest, and, in some cases, treatments have been ineffective [44-46]. For example, some data indicate that use of antipsychotics and benzodiazepines may actually precipitate delirium and contribute to further long term cognitive impairment[47,48]. Safe, efficacious, and cost-effective non-pharmacological treatments for delirium are urgently needed.

We have developed a theory-based intervention for DSD that is derived from the literature on cognitive reserve and based on our prior interdisciplinary work on delirium, recreational activities, and cognitive stimulation in people with dementia. Cognitive reserve is a construct used to explain the often noted lack of association between clinical manifestations of brain disease and actual brain pathology. It includes both passive and active processes that modify risk for the clinical expression of disease. Passive reserve, sometimes referred to as "brain reserve," is accounted for by brain size and synapse density[49]. It is hypothesized that individuals with larger brains and greater synapse density can tolerate more extensive pathology before they reach the threshold at which symptoms become clinically evident. Active reserve or "cognitive reserve," refers to the efficiency with which an individual can use alternate networks or cognitive strategies to cope with the brain pathology. Cognitive reserve is related to the brains metabolic activity[50] and is dynamic, active, and can be modified by mental activity. Brain reserve and cognitive reserve are not mutually exclusive. Mental activity is a strong signal for the generation of neurons and synapses[51] and, as discussed below, evidence for the ability to develop compensatory mechanisms in late life and early dementia is now emerging.

Epidemiological studies indicate that individual differences in cognitive reserve are due to life-time differences in mental activity; and these activities are considered markers of cognitive reserve. Individuals with more formal education, who are employed in occupations that are characterized by greater complexity and who engage in stimulating leisure activities appear to have greater cognitive reserve than those who participate in fewer mentally stimulating activities as evidenced by their lower risk for dementia and later manifestation of clinical symptoms when a dementia develops [52].

Studies have examined the association of markers of cognitive reserve and incident delirium. They indicate that individuals with low levels of educational attainment and deprivation (living alone) are at greater risk for delirium than individuals with more education or less deprivation[8,14,53]. Because education typically occurs in early life and is not the only source of mental activity over a lifetime, it is important to consider all forms of complex activities when assessing cognitive reserve[54]. A lifetime of low mental activity may lead to low cognitive reserve and increase vulnerability to noxious events that precipitate delirium.

Both delirium and dementia are conditions of reduced cognitive reserve[2,55,56] and have common risk factors: a lifetime of low engagement in complex mental activities[57] and presence of the ApoE *E4 allele[58]. Some investigators have suggested that because delirium and dementia share many clinical, metabolic, and cellular manifestations indicative of reduced cognitive reserve[55,59], they may be part of the same disorder[2,59]. It is plausible, then, that interventions that improve cognitive reserve in dementia may also be effective in delirium.

There is growing evidence that cognitively stimulating activities improve cognitive functioning in healthy older individuals and those in mild to moderate stages of dementia[60-63]. Cognitive stimulation is a specific form of cognitive-focused intervention, defined as a non-regimented intervention that involves engagement in a range of activities that promote cognitive processing aimed at general enhancement of mental and social functioning[64,65]. In this study we provide cognitive stimulation by using recreational activities that are tailored to individual interests and function and that encourage processing in the multiple cognitive domains affected by delirium.

A number of reviews and meta-analyses have assessed the effect of cognitive-focused interventions on cognitive function in older adults with dementia. Unlike in healthy populations, cognitive training has not received compelling support when used in people with dementia[66,67]. However, the benefits of cognitive stimulation for slowing cognitive decline in Mild Cognitive Impairment (MCI) and in mild to moderate stages of dementia are more robust[68-70]. In a trial that used mental status as primary outcome, effect sizes for cognitive gains associated with cognitive stimulation were comparable to those reported for the acetylcholinesterase inhibitors[62]. A recent meta-analysis of cognitive-focused interventions for dementia[71] found that cognitive stimulation had stronger effects for improving cognitive function than cognitive training. Outcome measures varied from study to study but included attention, orientation, memory, abstract thinking and executive functioning. Effects were greater when delivered in individual as opposed to group sessions. There is also some evidence that the effects of cognitive stimulation can be enhanced when combined with cholinergic drugs[72] but these effects deteriorate after one year of treatment[73]. Based on the evidence for the clinical and cost-effectiveness of cognitive stimulation, the National Institute for Health and Clinical Excellence in the U.K. has included this therapy in its guidelines for the non-pharmacological treatment of the cognitive symptoms of dementia[74].

Most of the research on the effects of cognitive stimulation has focused on the progression of dementia. Clinical observations[75] and our preliminary work[76] indicate that use of tailored cognitively stimulating recreational activities may also help resolve DSD. In two clinical trials[77,78] we demonstrated that we can capture and sustain attention in nursing home residents with dementia when we use recreational activities that match individual interests and abilities. Individual interests are important in the design of cognitive activities because when people with dementia are intrinsically motivated to participate in cognitive remediation they obtain greater cognitive and functional benefits[79]. Interesting and enjoyable activities facilitate cognitive processing in the cognitive domains affected by delirium: attention, orientation, memory, abstract thinking, and executive functioning[21]. Cognitive processing helps restore cognitive functioning[64,65], and in persons with delirium, improved cognitive function is accompanied by improvement in physical function[4,24] and resolution of delirium[22,80].

We conducted a pilot study to assess the feasibility of implementing our intervention in a post acute care setting with newly admitted patients who presented with DSD[76]. We provided cognitive stimulation by using recreational activities that were tailored to individual interests and function and that encouraged processing in the multiple cognitive domains affected by delirium. All participants had a diagnosis of dementia on admission and at least 2 symptoms of delirium as assessed by the Confusion Assessment Method [105]. We randomized 16 subjects to treatment with cognitively stimulating activities (N = 11) or usual care control (N = 5) and followed participants for 30 days. Blinded research assistants conducted daily assessments of delirium, delirium severity and functional status. Participants in the treatment group received activities for 30 minutes each day. Analyses indicated that the control group had a significantly greater decrease in physical function and mental status over time compared to intervention. Severity of delirium approached significance and improvement over time favored intervention. Although not statistically significant, there was a difference in mean (7.0 vs. 3.27) and median (7.0 vs. 3.0) days with delirium: the control group having more days of delirium. We were encouraged by these results and are ready to conduct a randomized clinical trial of treatment efficacy.

This paper describes the study protocol for our randomized clinical trial (RCT), referred to as Recreational Stimulation for Elders as a Vehicle to resolve DSD (RESERVE- DSD) in which we test these cognitively stimulating activities. The aims of the trial are: Aim 1) to demonstrate the efficacy of the RESERVE-DSD intervention for resolving delirium; Aim 2) to evaluate potential moderators (markers of cognitive reserve) of RESERVE-DSD efficacy; and secondary Aim 3) to describe the costs associated with implementing the intervention. Our hypothesized model of intervention effect is diagramed in Figure 1.

**Figure 1 F1:**
[figure not shown]
**Hypothesized Model**.

## Methods/Design

This randomized repeated measures clinical trial will involve participants being recruited and enrolled at the time of admission to post acute care, and then randomly assigned to one of two conditions: RESERVE-DSD (intervention) or usual care (control) (See Figure 2: Trial flow diagram.)The study protocol was approved by the Penn State Institutional Review Board (IRB# 33443). Participants in the intervention group will receive nursing care that is routinely delivered for their medical/surgical condition including participation in their prescribed therapies plus RESERVE-DSD. At the present time there is no standard care for DSD[43,81]. Participants in the usual care group will receive nursing care that is routinely delivered for their medical/surgical condition including participation in their prescribed therapies.

**Figure 2 F2:**
[figure not shown]
**Reserve-DSD Trial Flow Diagram**.

The two-group experimental design we propose may not completely control for the many variables that can affect DSD. We will control as much as possible for factors we believe are most likely to impact our findings through strict enrollment criteria, and by considering several potential covariates in our analyses: dementia stage, co-morbidities, age, use of CNS-active drugs, pain, infection, dehydration, APOE status, and lifetime complex mental activity including years of formal education, occupation, and past leisure activity.

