### Intervention

Participants in the intervention group will receive nursing care that is routinely delivered for their medical/surgical condition including participation in their prescribed therapies plus RESERVE-DSD. This intervention consists of increasingly challenging recreational activities that are cognitively stimulating and tailored to each participant's interests and functional abilities. The recreational activities target cognitive functions affected by delirium: attention, orientation, memory, abstract thinking, and executive functioning. Participants will receive up to 30 minutes of their respective recreational activities once a day between the hours of 1 pm and 5 pm for up to 30 consecutive days beginning within 24 hours of admission to post acute care.

The cognitively stimulating recreational activities to be studied are from previously designed, well-established programs of therapeutic activities from [name]'s research on the behavioral and cognitive symptoms of dementia, respectively. We have constructed a large base of cognitively stimulating recreational activities, many taken from the growing literature on brain fitness[75,86-90]. The activities, such as word search, finish the phrase, and name that tune, offer stimulation in multiple cognitive domains, combined in novel ways, as opposed to stimulation in a single cognitive domain like memory training.The investigators have classified the base of recreational activities by most prominent domain stimulated, however, in actuality activities stimulate several cognitive domains simultaneously. For example, the game of "Name that Tune" requires processing in the areas of both attention and memory. Multi-domain cognitive activities demonstrate more robust results than single domain training[91]. The activities are implemented using inexpensive items and are readily available to most nursing homes. Because they require no special expertise to implement, they are well-suited to the resource-stressed nursing home environment.

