### Description of Usual Care (Control)

At the present time there is no standard care for DSD [43,81]. Participants in the usual care group will receive nursing care that is routinely delivered for their medical/surgical condition including participation in their prescribed therapies. To describe what constitutes usual care (control) we will conduct medical chart reviews on all participants (intervention and control) and extract data on the following: attendance at prescribed therapies and activity programs; CNS-active drug use (regular and prn); and nursing interventions recorded for behaviors nurses use to describe delirium[100]: confusion, disorientation, altered mental status, agitation, inappropriate behavior, mental status change, inattention, hallucination, and lethargy. Because the nursing home environment is unstable[84,85], we will also record data every six months on staffing ratios at each site, as published on the Pennsylvania Department of Health website, and assess staff knowledge of delirium using our previously developed case vignettes[101]. We will ask all consenting staff (RN, LPN, and CNAs) to complete the vignettes at baseline and then every six months during data collection to capture any change in overall level of delirium knowledge per site that might occur due to historical factors or staff turnover in the nursing home. We will use these data to quantify usual care and to monitor any qualitative differences between sites.

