#### Measures of Variables Affecting Vulnerability

Dementia stage, age, comorbidity, pain, infection, dehydration and CNS-active drugs. Measures of these variables will be obtained during screening (dementia stage: Clinical Dementia Rating Scale), following consent at baseline (age, comorbidities: baseline chart review), daily (presence of pain), and weekly (infection, dehydration and CNS-active drugs: weekly chart review). We will use the *Charlson Co-morbidity Index*, a weighted index that takes into account the number and seriousness of co-morbid diseases, to calculate a co-morbidity score for each participant[121]. Pain will be measured daily using the Pain Assessment in Advanced Dementia *(PAINAD*) scale which is an observational scale of five items (breathing, vocalization, facial expression, body language, and consolability). We use an observational rather than a verbal scale for greater reliability on days when participants experience greater severity of delirium. *PAINAD *is scored from 0-10 and has an internal consistency reliability of 0.50-0.65 and interrater reliability of 0.82-0.97[122,123]. Infection and dehydration will be identified as present or absent (yes/no) during the weekly chart review. The trained RA will review new medical orders, lab values and nurses notes for indicators of infection and dehydration. CNS-active drugs can further cognitive deterioration because of their potent anticholinergic properties[35,36]. We identify CNS-active drugs administered through a weekly chart review using the American Hospital Formulary Service drug classification[36]. We then calculate the anticholinergic burden associated with these drugs using the *Anticholinergic Cognitive Burden *(ACB) Scale[124,125]. The ACB is an expert based practical index that classifies the severity of a drug's anticholinergic activity on cognition using a scale of 1 (mild), 2 (moderate) and 3 (severe). Total ACB is calculated by summing the ACB scores of all regularly and prn scheduled drugs administered to the participant for that week. We will weigh the ACB score for each drug by days administered during that week before summing for the total ACB score.

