### Statistical Analysis

Prior to conducting any statistical analyses, the distributions of all sample data will be examined. Extreme values will be compared with the original data collection forms in order to identify and correct data entry errors. Following this data validation step, sample distributions will be evaluated to determine if they meet the assumptions necessary for use of normal distribution-based statistical methods. If the data are not normally distributed, suitable transformations will be sought to normalize them. Possible transformations include log, square root, and rank transformations. If the data are not sufficiently normalized by transformation, the analysis may proceed using permutation testing to determine significance levels. Categorical variables will be evaluated using models based on the binomial or multinomial distributions. The design of this study is a two-group randomized design within blocks defined by individual nursing homes. Randomization will be conducted at the participant level, so that intervention groups are crossed with nursing homes, rather than nested within them. Repeated measurements will be made within individual participants for up to 30 days. The statistical methods must appropriately account for within-participant correlation among these repeated measurements.

The primary statistical model will be mixed-model analysis of variance (ANOVA). A term representing individual participants will be included as a random effect in the model in order to account for correlated multiple measurements for each participant. Treatment and covariates will be included as fixed effects. The primary outcome variables are delirium severity and duration, and cognitive and physical functioning.

The primary analyses will be based on intent to treat. Thus, participants will be included in the analyses regardless of their level of participation in the treatments or of their loss to follow-up. Participants who have missing data for some time points will not be excluded from analyses. The methodology incorporates all available measurements for each participant into the analysis. Missing values for some observation times will not cause the participant's entire record to be excluded from the analyses, as may occur in usual repeated measures models.

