Potential confounders will be included as covariates in the analysis. If a variable substantially alters either the significance level of a group comparison or a measure of association, that variable will remain in the model in order to control for its confounding effect. Variables that will be evaluated as covariates include those that increase delirium severity and duration, acetylcholinesterase inhibitors, and potential moderators of the association between treatment and outcome.

In order to evaluate differences in change across the study period between the intervention groups, time, and group by time interaction terms will be included in the model. A significant group by time interaction will be of interest, as it would reflect differences in rates of change between the groups. A significant interaction term could yield a non-significant test for the main effect of group, but could reflect an important effect of the intervention. If the test for interaction is significant, the nature of the interaction effect will be evaluated using means plots and post-hoc contrasts.

Hypothesized moderator variables will be evaluated using LISREL and SAS software. Structural models will be specified based on the path diagram presented previously. The path diagram will be used to define the hypothesized structure of the relationships among the variables. Multilevel structural equations modeling (SEM) will be used to evaluate the hypothesized structure, including testing the hypothesized moderator status of the cognitive reserve variables. Tests for moderation are based on regression relationships among the specified variables. These relationships are specified in the SEM model and may be tested based on statistical significance of parameters for direct and indirect effects in the hypothesized model. These relationships can also be tested using sets of mixed-model regression analyses[128-130]. This approach, based on the "Baron and Kenny steps"[128] will be implemented as supplemental analyses using SAS software. Using the regression approach, moderating effects are evaluated as the interaction effect of X and M. Least-squares means with 95% confidence intervals will be used to summarize moderated effects.

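### Covariates measured during treatment may enter the primary mixed model, and the retention rule favours keeping those that treatment has changed

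*Protocol article*

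**What the plan says.** In Methods/Design, the paragraph under Figure 2 names the factors to be considered as potential covariates. They include "use of CNS-active drugs, pain, infection, dehydration, APOE status, and lifetime complex mental activity".

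Measures of Variables Affecting Vulnerability gives the timing. Dementia stage is taken at screening, and two further items are taken "following consent at baseline (age, comorbidities: baseline chart review". The remaining four are collected "daily (presence of pain), and weekly (infection, dehydration and CNS-active drugs: weekly chart review". The drug variable is a weekly score: "Total ACB is calculated by summing the ACB scores of all regularly and prn scheduled drugs administered to the participant for that week", with each drug weighted by the days it was given.

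The Intervention section has sessions running "for up to 30 consecutive days beginning within 24 hours of admission to post acute care".

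Statistical Analysis states that "Treatment and covariates will be included as fixed effects" in the primary mixed model, that the primary analyses are by intent to treat, and that "Potential confounders will be included as covariates in the analysis". The candidates include variables that increase delirium severity and duration. A candidate stays in the model if it substantially changes either the significance level of a group comparison or a measure of association.

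Baseline Measures records all diagnoses and all prescribed medications from the chart after consent. No section says that these baseline records, rather than the daily or weekly ones, supply the covariate values.

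**The concern.** In a randomised comparison, a variable measured after treatment starts is not a confounder of the group effect. If treatment changes it, it is partly a result of treatment. Adjusting for it then does two things: it removes the part of the effect that passes through the variable, and it can introduce bias where an unmeasured factor, such as severity of the acute illness, drives both the variable and the outcome.

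Two routes are plausible here. CNS-active drugs, including those given as needed, may be used for the behaviours of delirium, and the Background says that they can themselves lead to delirium; an intervention that settles delirium could reduce their use. PAINAD scores vocalisation, facial expression, body language and consolability, which delirium may also alter. The route is weaker for infection and dehydration.

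At stake is the meaning of the primary group effect and group-by-time interaction for delirium, cognition and physical function. With such covariates in the model, neither need estimate the effect of assignment to RESERVE-DSD.

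**Working it through.** **1. Timing.** Sessions start within 24 hours of admission and last up to 30 days. Daily pain scores and weekly chart reviews over the same period are therefore almost all post-treatment values. The protocol separates baseline from on-study measures in one sentence and places these four variables on the on-study side. The weekly drug score, built from drugs administered in that week, is not a baseline quantity.

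**2. Selection.** A variable that treatment has changed and that also predicts the outcome will shift the group coefficient when added. The retention rule keeps variables for that reason, so it tends to select mediators.

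**3. Illustration of size.** The plan gives no figure to reproduce, and all inputs here are assumed. Let T be treatment, M the on-study covariate (within-arm SD 1) and U an unmeasured severity factor:

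- Y = −0.25T + 0.3M + 0.5U + error
- M = aT + λU + error
- Total effect = −0.25 + 0.3a
- Effect adjusted for M = −0.25 − 0.5λa

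| a | λ | Total | Adjusted | Reduction |
|---|---|---|---|---|
| −0.2 | 0.3 | −0.31 | −0.22 | 0.09/0.31 = 29% |
| −0.2 | 0.6 | −0.31 | −0.19 | 0.12/0.31 = 39% |
| −0.4 | 0.3 | −0.37 | −0.19 | 0.18/0.37 = 49% |
| −0.4 | 0.6 | −0.37 | −0.13 | 0.24/0.37 = 65% |

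A simulation with 2,000,000 participants gives −0.309/−0.218, −0.311/−0.191, −0.370/−0.191 and −0.372/−0.132, that is 29%, 39%, 48% and 65%. With a = 0 both expressions equal −0.25, so there is no bias. Without U, the reduction is 0.06/0.31 = 19% or 0.12/0.37 = 32%; the rest comes from the assumed severity factor.

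**4. At the trial's size.** With 256/2 = 128 per arm, and assuming two-sided 5% and 80% power (the article states neither), the detectable standardised difference is (1.960 + 0.842) × √(2/128) = 0.350. Take that as the total effect, with an M-to-outcome slope of 0.4. The unadjusted estimate stays near 0.35 with power about 0.79. Adjusted for M (4,000 simulated trials per cell):

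| Share of effect through M | Estimate (power), no shared cause | Estimate (power), shared cause loading 0.5 on each |
|---|---|---|
| 0% | 0.349 (0.85) | 0.351 (0.96) |
| 10% | 0.316 (0.78) | 0.294 (0.87) |
| 25% | 0.265 (0.63) | 0.208 (0.58) |
| 50% | 0.174 (0.31) | 0.065 (0.11) |

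Check of the 25% cell with a shared cause: a = 0.35 × 0.25/0.4 = 0.219, and 0.35 × 0.75 − 0.5² × 0.219 = 0.208.

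**5. No true effect on the outcome.** If treatment only shifts M, and M shares an unmeasured cause with the outcome, the absolute bias is loading² × shift. This runs from 0.5² × 0.2 = 0.05 to 0.7² × 0.5 = 0.245 SD, and simulated type I error runs from about 7% to 59% against a nominal 5%. When the shared cause pushes both the same way on a higher-is-worse outcome, a treatment that lowers M looks worse than it is, and one that raises M looks better.

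**The case against.** The protocol speaks of considering potential covariates and of evaluating them, so adjustment is conditional. It does not say whether a baseline, lagged or concurrent value would be used, and a journal article commonly leaves that to the full analysis plan. Baseline diagnoses and medications are collected, so baseline versions are partly available. These points stand: a reader might infer that the trial has already committed to on-treatment values of all four variables, and the text does not go that far. But this is more than missing detail. The stated timing, the construction of the weekly drug score and the stated retention rule together lead towards the problem.

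A reader might also infer that all four variables are consequences of treatment. The documents do not support this. They present the four as risk factors for delirium, and nowhere hypothesise that the activities change them. The causal route is an inference: plausible for drug use and observed pain, weak for dehydration, and not identified for infection.

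The record of "CNS-active drug use (regular and prn" under Description of Usual Care is collected to describe usual care in both arms. It shows that as-needed use is captured, not that it will be adjusted for.

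Finally, the percentages rest wholly on assumed inputs. A 0.4 SD shift in the covariate exceeds the assumed direct effect of 0.25. Comorbidity, dementia stage and age would capture some of the severity treated as unmeasured. The models use one continuous covariate at one time, whereas infection and dehydration are yes/no and the trial's model is longitudinal. All of this stands.

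**Conclusion.** The concern holds in a limited form. The stated rules allow covariates measured during treatment into the primary intent-to-treat model, and the retention rule favours those that treatment has affected. CNS-active drug burden and PAINAD pain matter most; infection and dehydration matter less.

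Whether bias would occur, and how much, cannot be read from the documents. It requires that RESERVE-DSD change the covariate; if it does not, adjustment is harmless and may add precision. The reductions of 29–39% and 48–65%, and the power and type I error figures, show what the mechanism can do under stated assumptions. A reader might take them as estimates of bias in this trial, which they are not. Because the issue touches every primary outcome, and a covariate set chosen after seeing its influence on the group comparison would be hard to defend, it should be settled before the outcome data are analysed.

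**What to change.** State that the primary model adjusts only for prespecified covariates recorded before the first session: dementia stage, age, comorbidity, APOE status, the Lifetime of Experiences score, medications and diagnoses from the baseline chart review, and the first PAINAD score if taken before any session. Assessments are in the morning and sessions in the afternoon, so such a score will often be available. Control participants have no sessions, so the cut-off should be worded to apply equally in both arms.

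Do not use the change-in-significance rule to bring post-randomisation variables into the primary model. Report on-study pain, infection, dehydration and anticholinergic burden by arm, or use them in a separately labelled exploratory or mediation analysis.

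The change is mainly one of wording and needs no larger sample. It explains slightly less outcome variance. Baseline medications are those prescribed, whereas the weekly score uses drugs administered, so the two are not interchangeable. Baseline infection and dehydration can be used only as far as the diagnoses in the admission chart show them, and a baseline value cannot represent an infection that arises later.
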